#### 2.1.2. Study Design Summary

Design type: Prospective, observational, non-randomised, non-blindedBlinding: PFT results will be blinded from the treating surgical team to avoid influencing management decisions. Investigators and participants will have access to clinical data.Control arm: Not applicableRandomisation: Not applicableSetting: Single tertiary NHS cardiac surgery centreRecruitment target: 100 patientsFollow-up: From preoperative baseline until 30 days post-CABG, with planned 1-year MACCE follow-up via digital health records

This design was chosen to capture the natural variability in platelet responsiveness and correlate these patterns with real-world surgical outcomes. Importantly, the study does not introduce any confounding influence of investigational treatments or unblinded interventions, ensuring validity in evaluating platelet function and postoperative risk stratification. Figure 1 summarizes the study design.

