#### 2.1.3. Treatment and Rationale

As a non-interventional observational study, no study-specific treatment will be administered, and participants’ standard perioperative and postoperative care will remain unaltered.

All antiplatelet therapy will be prescribed at the discretion of the treating surgical teams, following institutional protocols and national guidelines. The study does not involve randomisation, dose escalation, or therapeutic modifications based on PFT results. Instead, it aims to evaluate the association between naturally occurring variability in platelet reactivity and clinical outcomes under standard care conditions.

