#### 2.7.8. Secondary Endpoint Analysis

Analyses of secondary endpoints are exploratory and hypothesis-generating, as the study is not powered for statistical significance in these measures. Findings will guide future studies.

Variability in Platelet Function

Objective: Assess inter-individual variability in platelet inhibition across timepoints.Analysis:
Continuous values (% inhibition) summarized at baseline, discharge, and 6 weeksRepeated measures ANOVA or Friedman test for within-patient changesBoxplots and line graphs used for visualization

Prevalence of Platelet Resistance

Objective: Determine the proportion of patients with inadequate platelet inhibition.Analysis:
Categorical resistance status reported for each timepoint with 95% confidence intervalsChanges in resistance status analyzed using McNemar’s test for paired categorical data

Demographic and Clinical Predictors of Platelet Function

Objective: Explore associations between patient characteristics and platelet responsiveness.Analysis:
Univariable and multivariable linear regression for continuous % inhibition outcomesConsidered variables: age, sex, BMI, renal function, diabetes, and number of graftsSelection guided by clinical relevance and statistical significance (*p* < 0.1)

Impact of Platelet Resistance on Clinical Decision-Making

Objective: Evaluate whether platelet resistance influences treatment decisions, including DAPT use and discharge timing.Analysis:
Comparisons of DAPT prescription rates between resistant and non-resistant patients using chi-square or Fisher’s exact testLogistic regression to explore predictors of treatment decisions if data allows

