### 3.3. Secondary Analyses

Secondary analyses will investigate potential predictors of platelet function variability, including demographic and clinical factors such as diabetes status, renal function, smoking history, and surgical approach. Multivariable regression models will be employed to adjust for key covariates and assess independent associations with platelet responsiveness.

Additionally, the feasibility of integrating PFT into routine perioperative workflows will be examined. The study will evaluate whether PFT results influence clinical decision-making, including modifications in antiplatelet therapy or postoperative management.

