## 6. Study Limitations

As an observational study, this research does not involve direct therapeutic interventions by the study team. However, PFT results will be conveyed to the clinical team caring for the patient, who may modify treatment based on their clinical judgment. The study itself will generate valuable data regarding platelet function trends and potential predictors of poor outcomes, contributing to a better understanding of antiplatelet resistance without directly altering patient management within the study framework.

This study does not include immediate postoperative PFT upon arrival to the intensive care unit. While such measurements may offer mechanistic insights, discharge sampling was selected to balance clinical feasibility, patient safety, and assessment of stabilized platelet function following early recovery and antiplatelet therapy initiation.

Additionally, as with all studies incorporating PFT, variability in assay methodology and interpretation remains a challenge, given the lack of universal standardization across testing platforms [6]. Furthermore, the study is designed to evaluate platelet function within a defined perioperative timeframe, yet long-term outcomes beyond the study period may also be influenced by additional variables such as medication adherence, comorbid conditions, and secondary prevention strategies.

While venesection poses minimal risk, the additional blood sampling may introduce slight inconvenience for participants, although efforts have been made to integrate sample collection within routine clinical care.

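### Section 2.1.2 withholds platelet function results from the treating team while Section 6 passes them on and allows treatment changes, so the conduct behind the primary association is contradictory

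*Protocol article*

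**What the plan says.** All references are to the protocol article.

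- **Section 2.1.2** sets the access rule: "PFT results will be blinded from the treating surgical team to avoid influencing management decisions". It then argues that "the study does not introduce any confounding influence of investigational treatments or unblinded interventions", and treats this as securing the validity of the evaluation. The same list labels the design as not blinded.
- **Section 2.1.3** says participants' standard care is left as it is, and that "The study does not involve randomisation, dose escalation, or therapeutic modifications based on PFT results". It names the prescribers: "All antiplatelet therapy will be prescribed at the discretion of the treating surgical teams". It also gives the target: "it aims to evaluate the association between naturally occurring variability in platelet reactivity and clinical outcomes under standard care conditions".
- **Section 6** says: "PFT results will be conveyed to the clinical team caring for the patient, who may modify treatment based on their clinical judgment".
- **Section 3.3** plans a secondary analysis: "The study will evaluate whether PFT results influence clinical decision-making, including modifications in antiplatelet therapy or postoperative management".
- **Section 2.7.8** has a related objective: "Evaluate whether platelet resistance influences treatment decisions, including DAPT use and discharge timing". It is analysed by comparing DAPT prescription rates between resistant and non-resistant patients.

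**The concern.** Withholding the results and releasing them produce different data. If the team never sees the results, the link between resistance and later events describes prognosis under usual care, which is the aim in Section 2.1.3. If the team sees them and may act, resistant patients can be treated differently because they tested resistant. The association then mixes the prognosis of resistance with the effect of whatever was done about it.

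The contradiction touches the primary analysis. It also bears on day-to-day conduct: staff could follow either section, or follow one for some patients and the other for others. Once data have been collected under a mixture, no analysis could cleanly separate the two.

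**Working it through.** The plan states no figure on this point, so there is none to reproduce. The check is a comparison of the text, followed by an illustration on assumed inputs.

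**Step 1: can both access rules hold?** They could only if the team in Section 2.1.2 and the team in Section 6 were different people. The article never distinguishes them, and Section 2.1.3 gives antiplatelet prescribing to the treating surgical teams, the group said to be blinded. Even with two separate teams, treatment changed on a test result would conflict with Section 2.1.3, which leaves standard care unchanged.

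**Step 2: which planned analyses need disclosure?**
- Section 3.3 asks about the influence of the test results. Clinicians cannot be influenced by results they do not see, so this analysis presupposes release.
- Section 2.7.8 compares DAPT rates by resistance status. This can be computed under either rule. If results are withheld, a difference would reflect patient characteristics or drug exposure, so only the claim of influence fails.

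**Step 3: can disclosure reach the primary outcomes?** Section 2.5.1 places tests on the morning before surgery, at discharge (day five to seven, or earlier if discharged sooner) and at six weeks. MACCE is assessed at 30 days and one year (Section 1).
- A baseline result can affect care before almost all postoperative events.
- A discharge result can affect only events after discharge.
- A six-week result comes too late for 30-day MACCE but precedes most of the one-year window.

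**Step 4: does the planned model deal with it?** The logistic regression in Section 2.7.4 names age, diabetes, renal function and surgical factors. A treatment change prompted by the result is not among them. Adding it as an ordinary confounder would not solve the problem, because it would lie between exposure and outcome. The same applies to Section 2.1.4, which treats recorded concomitant medication as potential confounders.

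**Step 5: illustration.** None of these inputs is in the documents:
- p0, event risk in non-resistant patients: 5% or 10%
- true odds ratio (OR) under withheld results: 2.0 or 3.0
- f, share of resistant patients whose treatment is changed: 25%, 50% or 75%
- effect of the change: risk returns fully to p0

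Formulas:
- p1 = OR·o0 / (1 + OR·o0), with o0 = p0/(1 − p0)
- q = p1(1 − f) + p0·f
- observed OR = [q/(1 − q)] / o0

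Worked case with p0 = 10%, OR = 2.0, f = 50%: o0 = 0.1111; p1 = 0.2222/1.2222 = 18.18%; q = 0.5 × 18.18% + 0.5 × 10% = 14.09%; observed OR = (0.1409/0.8591)/0.1111 = 1.48.

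| p0 | True OR | f = 25% | f = 50% | f = 75% |
|---|---|---|---|---|
| 5% | 2.0 | 1.74 | 1.49 | 1.24 |
| 10% | 2.0 | 1.73 | 1.48 | 1.23 |
| 5% | 3.0 | 2.46 | 1.95 | 1.47 |
| 10% | 3.0 | 2.43 | 1.91 | 1.43 |

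If the change removes only a fraction e of the excess risk, f is replaced by f·e. For example, 50% switched with half the excess removed equals the 25% column (0.5 × 0.5 = 0.25).

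**The case against.** The best defence is the distinction that Section 6 itself draws: the study team does not intervene, and any change is the clinicians' own judgment. On that reading the sentence in Section 2.1.3 excludes only changes required by the study and is compatible with Section 6. This part stands for that sentence. It does not rescue Section 2.1.2, which withholds results precisely so that management is not influenced, nor the statement in Section 2.1.3 that care is left as it is. The bias also does not depend on who orders the change.

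The not-blinded label adds little, since it may simply mean that there is no masked treatment.

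Several stronger readings are tempting, and the documents do not support them:

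- *The study's question is undefined.* Sections 2.1.2 and 2.1.3 state it; only the conduct is unsettled.
- *Section 2.1.3 also claims blinding and freedom from confounding.* Both claims are in Section 2.1.2 only.
- *The Section 2.7.8 comparison is impossible under blinding.* It can be computed and the section calls it exploratory; it needs rewording, not deletion.
- *The bias runs toward no effect throughout.* That is plausible for MACCE. For bleeding, intensified treatment in resistant patients could move the association either way, even creating one. Results also cannot alter care for events that precede them.

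**Conclusion.** The point holds as a contradiction in current text. Section 2.1.2 and Section 6 give opposite access rules, Section 3.3 depends on the second, and no passage reconciles them. Under the Section 6 rule the validity argument in Section 2.1.2 no longer holds, and the primary association would be one observed under disclosed results, not the one targeted in Section 2.1.3.

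The size of the bias cannot be derived from the documents. With the assumed 5–10% risk and a true odds ratio of 2.0, the observed value is about 1.7, 1.5 and 1.2 at 25%, 50% and 75% switching. Full efficacy makes these the largest attenuation at each share, provided the change does not take risk below that of non-resistant patients. A reader might infer that a real doubling of the odds would be all but erased. That needs both very frequent switching and a fully effective change, and the documents give neither. The case for correction rests on the contradiction, not on these figures.

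**What to change.** State one rule on release of platelet function results, applied to all patients, and bring Sections 2.1.2, 2.1.3, 2.7.8, 3.3 and 6 into line with it. Which rule applies is a decision for the investigators; each has consequences for the analysis.

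- **If results are withheld:** remove the disclosure sentence from Section 6 and the analysis in Section 3.3 of whether results influence decisions. Reword the DAPT comparison in Section 2.7.8 as a description of treatment by resistance status, not as an influence of the test.
- **If results are released:** remove the blinding statement and the claim of no confounding influence from Section 2.1.2, and the statement in Section 2.1.3 that care is left unchanged. Record the date of each disclosure and any treatment change that follows from it. Report the primary association as one under disclosed results.

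The cost is protocol wording and a local instruction on release of the TEG6s results. Withholding also loses one secondary analysis (Section 3.3); release adds the recording of disclosures and resulting changes.

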#### 2.1.3. Treatment and Rationale

As a non-interventional observational study, no study-specific treatment will be administered, and participants’ standard perioperative and postoperative care will remain unaltered.

All antiplatelet therapy will be prescribed at the discretion of the treating surgical teams, following institutional protocols and national guidelines. The study does not involve randomisation, dose escalation, or therapeutic modifications based on PFT results. Instead, it aims to evaluate the association between naturally occurring variability in platelet reactivity and clinical outcomes under standard care conditions.

#### 2.1.4. Standard Medications Permitted

Patients undergoing elective and urgent CABG are expected to receive the following standard antiplatelet regimens:Aspirin (typically 300 mg within 6 h of return from operating theatre followed by 75 mg once daily)Clopidogrel (typically 75 mg once daily, when prescribed)

Additionally, concomitant medications—including beta-blockers, ACE inhibitors, statins, or anticoagulants (such as warfarin or direct oral anticoagulants, DOACs)—may be prescribed as per clinical indications. These will be recorded and accounted for in the final analysis as potential confounding variables affecting platelet function and surgical outcomes.

#### 2.1.5. Significance of Study Design

This observational study provides foundational data to support the development of future clinical trials aimed at tailoring antiplatelet therapy based on individual platelet function profiles. By prospectively assessing platelet responsiveness at multiple perioperative timepoints, the study seeks to improve risk stratification, optimize therapeutic decision-making, and contribute to evolving guidelines for antiplatelet management in CABG patients.

### 2.2. Study Setting

This study will be conducted at Harefield Hospital, a leading UK cardiac surgery centre. The recruitment and clinical assessments will be performed within routine perioperative pathways, ensuring that participation does not interfere with standard patient care.

### 2.3. Participant Recruitment

Eligible patients will be identified during preoperative surgical planning, typically one to three days before their scheduled coronary artery bypass grafting. The study team will liaise with surgical and pre-assessment clinic staff to screen upcoming cases against inclusion and exclusion criteria.

Potential participants will be approached by a member of the clinical team, who will provide verbal and written information about the study. Patients will be given the Participant Information Sheet and allowed at least 24 h to consider participation unless an expedited timeline is required due to urgent surgery scheduling. Written informed consent will be obtained before any study-specific procedures, including blood sampling for PFT.

### 2.4. Eligibility Criteria

#### 2.4.1. Inclusion Criteria

Adults aged 18 years or olderScheduled for elective or urgent, isolated coronary artery bypass grafting at the study centreExpected to receive standard antiplatelet therapy (aspirin or dual antiplatelet therapy) postoperatively as part of routine careAble and willing to provide written informed consent to participate in the studyWilling to undergo perioperative blood sampling for PFT as per the study protocolAble to understand and comply with study procedures and follow-up requirements

#### 2.4.2. Exclusion Criteria

Participants will be excluded if they meet any of the following criteria:Known diagnosis of a platelet function disorder or coagulopathy (e.g., Glanzmann thrombasthenia, von Willebrand disease, myelodysplasia)Current use of investigational drugs or devices or participation in another interventional clinical trial within thirty days prior to enrolmentRecent treatment within seven days with glycoprotein IIb/IIIa inhibitors (e.g., abciximab, eptifibatide), ticagrelor, prasugrel, or regular NSAIDs beyond low-dose aspirinPregnancy or breastfeeding at the time of consentPositive pregnancy test within seven days prior to enrolment in women of childbearing potentialInability or unwillingness to provide written informed consentSevere anaemia with haemoglobin less than eight grams per decilitre or thrombocytopaenia with platelet count below one hundred times ten to the power of nine per litre at baselineAny condition or concurrent illness that, in the investigator’s opinion, would compromise patient safety or impair the ability to comply with study procedures

### 2.5. Study Procedures

#### 2.5.1. Platelet Function Testing

Platelet function will be assessed using TEG6s Platelet Mapping (Haemonetics), a viscoelastic assay that quantifies platelet inhibition in response to aspirin and clopidogrel therapy. Testing will be performed at three perioperative timepoints:Baseline PFT will be performed on the morning before surgery.Discharge at postoperative day five to seven. For patients discharged earlier than postoperative day five, testing will be undertaken prior to discharge.Six-week follow-up visit

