#### 2.5.3. Clinical Outcomes and Follow-Up

Participants will be followed from preoperative baseline through twelve months postoperatively, capturing routine clinical outcomes including:Major adverse cardiovascular and cerebrovascular events, including myocardial infarction, stroke, and cardiovascular deathPostoperative bleeding, defined as Bleeding Academic Research Consortium type two or higherNeed for surgical re-exploration for haemostasisTransfusion requirements, including blood product administrationDuration of hospital stay, including intensive care unit and ward admissionWound healing and postoperative complications

Follow-up visits will occur at discharge between postoperative day five and seven, at six weeks postoperatively, at thirty days via telephone contact, and at twelve months through digital health records review.

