## 4. Discussion

This study aims to address the critical challenge of antiplatelet resistance in patients undergoing coronary artery bypass grafting (CABG). Despite the widespread use of dual antiplatelet therapy, a significant proportion of patients exhibit laboratory-confirmed resistance to aspirin and/or clopidogrel. This resistance, whether transient due to perioperative platelet turnover or persistent due to genetic, metabolic, or inflammatory mechanisms, has been associated with adverse cardiovascular outcomes such as graft occlusion, myocardial infarction, and increased mortality risk [5,6].

Current guidelines do not recommend routine PFT for CABG patients, primarily due to a lack of high-quality prospective data correlating platelet reactivity profiles with postoperative outcomes [9,10]. As a result, postoperative antiplatelet management remains largely empirical, contributing to variability in prescribing practices and uncertainty regarding the role of PFT [8]. The present study seeks to address this gap by prospectively evaluating perioperative platelet reactivity and correlating these findings with clinical outcomes to determine whether PFT can serve as a reliable risk stratification tool for CABG patients.

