## 5. Potential Implications

By systematically assessing platelet function in the perioperative period, this study may provide critical insights into the prognostic relevance of antiplatelet resistance. Prior observational research suggests that pre- and postoperative platelet reactivity profiles may serve as early indicators of risk, enabling clinicians to identify patients at heightened risk for ischemic complications [5,11]. Additionally, studies have demonstrated that conventional aspirin doses (100 mg daily) may be insufficient in suppressing thromboxane synthesis in the early postoperative period due to accelerated platelet turnover [11,12]. The potential for transient resistance to resolve spontaneously, as reported in previous investigations, highlights the dynamic nature of platelet responsiveness and underscores the importance of individualized antiplatelet strategies [12].

Beyond individual risk stratification, the findings from this study may inform broader clinical practice by guiding the development of personalized antiplatelet regimens tailored to patients’ pharmacodynamic profiles. Previous studies, such as the BOCLA-Plan and tailored dual antiplatelet strategies using CYP2C19 genotyping, have demonstrated that dose adjustments or alternative antiplatelet agents can effectively overcome resistance [13,14]. If the present study validates the predictive utility of PFT, it could provide the foundation for future randomized trials evaluating personalized antiplatelet approaches, ultimately improving outcomes in CABG patients.

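### The early postoperative platelet test is scheduled by discharge, so recovery helps set the test day and can bias this test's association with in-hospital outcomes

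*Protocol article*

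**What the plan says.** Section 2.5.1 gives three test times: the morning before surgery, discharge, and the six-week visit. The middle one reads "Discharge at postoperative day five to seven", followed by "For patients discharged earlier than postoperative day five, testing will be undertaken prior to discharge". Section 2.5.3 repeats the link: "Follow-up visits will occur at discharge between postoperative day five and seven". Neither section sets an earliest day, and neither covers a patient still in hospital after day 7.

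Three other places bear on whether the day matters:

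- Section 4 describes the condition being measured: "This resistance, whether transient due to perioperative platelet turnover or persistent due to genetic, metabolic, or inflammatory mechanisms".
- Section 5 says standard aspirin dosing may suppress thromboxane insufficiently "in the early postoperative period due to accelerated platelet turnover", and adds "The potential for transient resistance to resolve spontaneously".
- Section 6 gives the reason for the timing: "discharge sampling was selected to balance clinical feasibility, patient safety, and assessment of stabilized platelet function following early recovery".

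On analysis, section 2.7.4 models events on resistance status, adjusting for age, diabetes, renal function and surgical factors. Section 2.7.8 summarises % inhibition at baseline, discharge and 6 weeks, tests within-patient change, and compares paired resistance status by McNemar's test. It also states an objective to "Evaluate whether platelet resistance influences treatment decisions, including DAPT use and discharge timing". The day of testing appears in none of these.

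**The concern.** A patient who recovers quickly is tested early, and a patient who bleeds, is re-explored or is otherwise delayed is tested later. If platelet response is still changing over those days, as the article's own account of transient resistance suggests, part of any difference between patients with and without complications reflects the calendar and not the patient.

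The direction can mislead either way. If inhibition rises as early turnover settles, delayed patients look better inhibited. That could create an apparent link between stronger inhibition and bleeding, or mask a real link between weak inhibition and an adverse event.

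The test matters because it is the only postoperative reading before six weeks. In the trend and McNemar analyses, readings from different recovery days would be pooled as one timepoint. The early-discharge rule also sits uneasily with the reason given in section 6, since the earliest leavers are sampled when function has had least time to settle.

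**Working it through.** The article states no figure on test timing, so there is none to reproduce. The check asks how large a false association the stated rule could produce.

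**Input from the article:** target of 100 patients (section 2.1.1).

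**Assumptions, not in the article:** 30% of patients complicated; discharge evenly spread over days 6 to 10 for them and days 4 to 6 for the rest; between-patient SD of 20 points of % inhibition; inhibition rising by b = 2, 3 or 5 points per day; no true association.

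**Spurious difference** = b × (mean test day, complicated − mean test day, uncomplicated) / 20.

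The text allows three readings:

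1. *Testing follows actual discharge.* Mean days 8 and 5, gap 3. Differences: 2×3/20 = 0.30, 3×3/20 = 0.45, 5×3/20 = 0.75 SD.
2. *Testing capped at day 7.* Complicated mean (6 + 4×7)/5 = 6.8; gap 6.8 − 5 = 1.8. Differences: 0.18, 0.27, 0.45 SD.
3. *Testing on day 5, or at discharge if earlier.* Means 5 and (4+5+5)/3 = 4.67; gap 0.33. Differences: about 0.03, 0.05, 0.08 SD.

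**False-positive rate.** For 30 against 70 patients, a shift of d SD moves the test statistic by about d × √(30×70/100) = 4.58d. At d = 0.27 this is 1.24, giving a rejection rate of about 24%. Simulation (3,000 runs, two-sided 5% t-test) gives:

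| Reading | b = 2 | b = 3 | b = 5 |
|---|---|---|---|
| Actual discharge, to day 10 | 26% | 53% | 91% |
| Capped at day 7 | 13% | 22% | 52% |
| Day 5 or earlier discharge | 5% | 6% | 7% |

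I repeated these runs and agree to within about 2 percentage points. With test day added to the model, the rate is about 5% under every reading.

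**Second set of assumptions** (25% complicated; stays of 3 to 7 days without and 5 to 10 with a complication; drift of 0.1, 0.2 or 0.3 SD per day; 4,000 runs). False-positive rates are 10.9%, 28.0% and 51.7% capped at day 7; 18.0%, 52.3% and 82.3% at actual discharge; and 4.7%, 6.6% and 8.8% on day 5 or earlier discharge.

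**Masking.** In this second set, capped at day 7, a true difference of −0.5 SD is observed as −0.33, −0.17 and −0.01 SD. The chance of detecting it falls from 56% with no drift to 29%, 11% and 4%. Adjusting for test day recovers only about 41%, because day and complication are correlated. Testing everyone on one day gives about 57% (run at 0.2 SD per day).

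**The case against.** The strongest reply is that the problem is bounded and its size is assumed. Both sections that schedule the visit name day 5 to 7, and read as a firm window this rules out testing to day 10. The article gives no change in inhibition per day. Saying that resistance may be transient does not say that it moves materially between days 4 and 7, and section 6 says the timing was chosen for stabilised function. Recording the sample date and adjusting for it are also details commonly left to a full protocol or SAP, and the mixed models in section 2.7.4 could use actual time.

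Much of this stands. The day-10 figures are one reading of an ambiguous rule, and the drift is an inference. What does not fall away is the rule itself, which the article states: test day moves with discharge, without a lower limit and with the upper limit unclear. An analysis plan could add test day, but at some loss of precision, and it cannot supply comparable readings where early test days occur only in good recoverers.

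Three stronger inferences are not supported:

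- *That later MACCE is shown to be biased.* The simulated complication is the one that delays discharge. Bias for later events needs a further link from early complications to those events, which is plausible but was not calculated.
- *That a planned length-of-stay analysis is distorted.* Length of stay is captured in section 2.5.3, but no analysis of platelet results against it is specified.
- *That the discharge-timing aim in section 2.7.8 is circular.* It is circular only if the discharge test is the one used, which the section does not say. The comparison it does specify concerns DAPT prescription rates.

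**Conclusion.** The concern holds in limited form. Tying the early postoperative test to discharge lets recovery help set the test day. If platelet response is still changing, that can bias this test's association with bleeding, re-exploration and transfusion, and it blurs the discharge timepoint in the trend and McNemar analyses.

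The size cannot be read from the article. On the assumptions above, it runs from negligible when nearly everyone is tested on day 5, through a moderate to large effect with a cap at day 7, to severe only if testing follows actual discharge to day 10. A reader might take the 91% as the expected error rate; it is the extreme of an assumed range. Worth correcting before recruitment; confidence is moderate.

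**What to change.** - In section 2.5.1, anchor the second test to one prespecified postoperative day within the existing window, for example its opening day, for every patient still in hospital, ready to leave or not. Align section 2.5.3. This also settles what happens to patients staying beyond day 7.
- Keep pre-discharge sampling only for patients who leave before that day.
- Record the actual test day, include it as a covariate in every analysis that uses this test, and add a sensitivity analysis excluding samples taken off the prespecified day.
- Where discharge timing is examined under section 2.7.8, relate it to the baseline test and not to the discharge test.

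The number of samples does not change. The cost is revised wording, one date field, one extra model term and slightly less freedom in scheduling. Early leavers will still be sampled earlier, so a small residual dependence remains; the covariate and the sensitivity analysis are there to deal with it.
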